***Cervical Biopsies Reporting***

The cervical biopsy specimens and the biopsy request will be sent to the Cervical Screening Laboratory. After specimen identification and labeling, the specimens and forms with accession number will be transferred to the Histopathology Laboratory, the University of Hong Kong. The tissue will undergo procedures to produce thin sections for microscopic examinations, inlcuding tissue processing, embedding, microtome sectioning, and Haematoxylin and Eosin staining.

The pathologists on duty may be requested to perform macroscopic description and cut up for bigger specimens such as loop excision. After tissue processing, histology slides and the forms are then returned to the office of Cervical Screening Laboratory for distribution to pathologists on duty. The macroscopic and microscopic descriptions as well as diagnosis are entered into the same laboratory information system.

**Outcome Measures**

Histological CIN2, CIN3 and cervical cancer are the primary outcomes of the study. Diagnosis will be obtained through biopsies. Secondary outcomes include (1) HPV prevalence at baseline, (2) HPV clearance or persistence among participants who test positive at baseline, (3) clearance of mild cervical abnormalities among participants who test HPV negative and (4) sensitivities, specificities, predictive values of the two screening methods.

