**METHODOLOGY**

**Study Aim**

To compare HPV-cytology co-testing with cytology testing in primary cervical screening for the detection of high grade cervical intraepithelial neoplasia (CIN2 or higher) among Hong Kong Chinese women aged 30 years or above.

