**Hypotheses**

- There is a significant difference in the number of CIN2+ cases detected between the cytology testing group and the cytology-HPV co-testing group at baseline.
- Significantly more CIN2+ cases will be detected at the second round of screening among participants with normal cytology result in the control arm than those with normal cytology and negative HPV results in the intervention arm.
- Cases infected by certain HPV genotypes are at higher risk of developing CIN2+ or HGSIL than those infected by other HPV genotypes.

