**Sample Size Calculation**

Based on the 2004-07 registry data from the Department of Health’s Cervical Screening Programme, the local prevalence of CIN2+ was postulated to be about 1.2%. A total sample size of 12000 women will be required to detect an absolute difference of 25% in the sensitivity between the control arm and the intervention arm in the detection of CIN2+ at 80% power and alpha = 0.05 (2-sided) and to account for an estimated 10% lost to follow-up rate.

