**Data analysis**

Data analysis will be performed according to the intention-to-treat principle. For proportion comparisons, chi-square tests will be employed. At baseline, logistic regression will be used to determine the associations between cervical cancer risk factors and HPV infection or cervical abnormalities. HPV prevalence will be calculated for participants in the intervention group. HPV clearance or persistence will be obtained by comparing those participants who have a positive HPV result at baseline and who do not require treatment for cervical lesions with their subsequent HPV testing results at 1-year post colposcopy. Clearance of mild cervical abnormalities will be obtained based on the participants with borderline cytology results at baseline and the proportion of these same participants who turn normal at subsequent screening without ever requiring treatment for cervical precancerous lesions if present. Incidence of CIN2+ will be calculated for both arms at baseline and at the second screening round. The estimated relative risks of CIN2+ will be calculated and compared at the second screening round for the control arm participants who have normal cytology results and for those in the intervention arm who have normal cytology and negative HPV results at baseline, respectively. Sensitivities, specificities, predictive values of the two screening methods for the detection of CIN2+ will be calculated based on the cervical biopsy data from participants who undergo colposcopy at baseline.

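### The protocol does not fix one primary outcome, round and contrast: the outcome list, the hypotheses and the sample size each point to a different one, and testing CIN2+ at both rounds at 0.05 gives a family-wise error of up to 9.75%

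*Protocol*

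**What the plan says.** Four sections of the protocol bear on what decides the trial.

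- **Study Aim.** The comparison is "for the detection of high grade cervical intraepithelial neoplasia (CIN2 or higher) among Hong Kong Chinese women aged 30 years or above". This is a composite, and no screening round is named.
- **Outcome Measures.** "Histological CIN2, CIN3 and cervical cancer are the primary outcomes of the study". The list is plural and gives no time point. Sensitivities, specificities and predictive values are the fourth secondary outcome.
- **Hypotheses.** Three bullets stand at the same level. The first is "There is a significant difference in the number of CIN2+ cases detected between the cytology testing group and the cytology-HPV co-testing group at baseline". The second is "Significantly more CIN2+ cases will be detected at the second round of screening among participants with normal cytology result in the control arm", compared with intervention-arm women who were negative on both tests. The third concerns genotypes: "Cases infected by certain HPV genotypes are at higher risk of developing CIN2+ or HGSIL than those infected by other HPV genotypes".
- **Sample Size Calculation.** A total of 12000 women is justified by a 25-point difference in sensitivity for CIN2+ at "80% power and alpha = 0.05 (2-sided"), with 1.2% prevalence and 10% loss. This is the only alpha in the document.

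The Data analysis section plans chi-square tests for proportions and adds: "Incidence of CIN2+ will be calculated for both arms at baseline and at the second screening round". It does not mark either round as primary.

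**The concern.** A reader who wants to know which result makes the trial positive gets three answers: individual histological grades (Outcome Measures), CIN2+ at either of two rounds (Hypotheses), and sensitivity (Sample Size Calculation).

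The choice matters because the two CIN2+ comparisons answer different questions, and co-testing is favoured by opposite signs. At baseline a benefit shows as more CIN2+ in the intervention arm. At the second round it shows as less CIN2+ among women who had screened negative. If one comparison is significant and the other is not, the protocol has no rule for the conclusion. If either may carry the claim at the full 0.05, the type I error exceeds the stated level.

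**Working it through.** **Step 1. What the stated sample size is for.** The protocol gives a 25-point sensitivity gap, 80% power, two-sided alpha 0.05, 1.2% prevalence, 10% loss and 1:1 allocation. It does not give the two sensitivities, so I assume 50% v 75%.

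Cases per arm without continuity correction:

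n = [1.96·√(2·0.625·0.375) + 0.842·√(0.5·0.5 + 0.75·0.25)]² / 0.25² ≈ 57.7, rounded up to 58.

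With continuity correction this becomes 66. The number of women is 2 × 66 / 0.012 = 11000. Allowing for loss gives 11000 / 0.9 = 12222, or 11000 × 1.1 = 12100. Both are within 3% of the stated 12000.

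The other control-arm sensitivities tried, from 30% to 70%, gave totals of about 6,700 to 12,960 (two-sided, divided by 0.9), none within 3%. So 12000 is reproduced as a comparison of sensitivity among CIN2+ cases, with the whole 0.05 spent on that one contrast. It is not sized for the number of CIN2+ cases detected per woman randomised, which is what Hypothesis 1 compares.

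**Step 2. Error if either CIN2+ hypothesis counts as success.** The protocol does not state this rule; it is the reading under test. The tests are taken as independent, which gives the largest value.

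| What counts as a false claim | Formula | Result |
|---|---|---|
| Either test significant, either direction | 1 − 0.95² | 9.75% |
| Hypothesis 1 either direction, Hypothesis 2 only as stated | 1 − 0.95 × 0.975 | 7.4% |
| Either test significant in favour of co-testing | 1 − 0.975² | 4.9% (one test: 2.5%) |
| Both tests required, either direction | 0.05² | 0.25% |

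A null simulation of the chi-square tests (400,000 runs; assumed CIN2+ rates 0.9% at baseline and 0.4% at round 2) gave 9.7% for the first row and 7.3% for the second. If the two test statistics were correlated, the first row would fall to 9.1% at correlation 0.5 and 7.8% at 0.8.

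**Step 3. Error after repair.** Under Holm, a false rejection when both nulls are true requires the smaller p to be at or below 0.025: 1 − 0.975² = 4.94%. A pre-stated order holds the error at 5% or less.

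**Step 4. Power of Hypothesis 1 as written.** The detected rate is 0.012 × sensitivity, with 6000 per arm and two-sided 0.05.

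- 50% v 75%: 0.60% v 0.90%. z = [0.0030·√6000 − 1.96·√(2·0.0075·0.9925)] / √(0.006·0.994 + 0.009·0.991) ≈ −0.06, so power is about 48%.
- 65% v 90%: 0.78% v 1.08%. The same formula gives about 40%.

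At Holm's first threshold of 0.025 these become about 37% and 30%. The stated 80% therefore does not carry over to the baseline CIN2+ comparison.

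**The case against.** **The outcome list is only a loose way of writing CIN2+.** This largely stands. The Study Aim, both CIN2+ hypotheses, the sample size and the analysis section all use the composite, and participation ends at CIN2 or greater in both arms. A reader might infer that three outcomes tested at two rounds make six tests, with an error of 1 − 0.95⁶ = 26.5% if independent. The documents do not support that, because no section plans a separate test of CIN2, CIN3 or cancer. What remains is that the outcome list should say it is a composite and give a time point.

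**Multiplicity control belongs in a statistical analysis plan.** This is fair, and the absence of an adjustment method is not the finding. The finding is that the protocol does address its primary outcome, contrast and sized quantity, and does so inconsistently.

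**Nowhere does the protocol say that success on either hypothesis suffices.** This is correct. All the inflated figures in Step 2 are conditional on that reading. It is also correct that 9.75% counts results against co-testing; the false-superiority figure is 4.9%.

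**The two rounds would often disagree.** A reader might infer that the missing rule would decide about half of all trials. Simulation does show exactly one test significant in 47–51% of trials, taking 1.2% prevalence and sensitivities from 50 v 75% to 65 v 90%, with 70% of missed lesions persisting and 0.1–0.3% new CIN2+. Under those inputs, however, Hypothesis 1 has about 40–48% power and Hypothesis 2 about 29–53%, so one significant and one non-significant result is mostly what two underpowered tests produce. It is not evidence that the rounds conflict, and the persistence and new-lesion rates are not in the documents.

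**Conclusion.** The point holds as an internal inconsistency in the protocol. Outcome Measures, Hypotheses and Sample Size Calculation do not identify the same primary contrast, and the sized quantity is one that the protocol itself calls secondary.

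The cost in error rate is moderate and conditional: at most 9.75% if either CIN2+ hypothesis may carry the claim in either direction. It is smaller if Hypothesis 2 counts only as worded, if the tests are correlated, or if only claims favouring co-testing are counted. The error formulas need no event rates. The power figures in Step 4 rest on the protocol's 1.2% prevalence and 25-point gap and on assumed sensitivities.

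The documents do not show that the trial intends to claim success from any single grade, or that baseline rather than the second round is meant to decide. The Study Aim names no round.

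**What to change.** - **Outcome Measures:** state one primary outcome, histological CIN2+ (CIN2, CIN3 or cancer), compared between the randomised arms. Label the separate grades exploratory.
- **Hypotheses and Data analysis:** control alpha across Hypotheses 1 and 2 with Holm (smaller p tested at 0.025, then the other at 0.05). Alternatively, the sponsor names the deciding round in advance and makes the other the key secondary. Label Hypothesis 3 exploratory.
- **Sample Size Calculation:** state the two assumed sensitivities, and make the sized quantity and the stated power refer to the declared primary contrast.

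The first two changes need no extra participants or procedures, but they have a price. A claim from a single round faces a stricter threshold. The 80% power must also be restated: for a baseline CIN2+ comparison with 6000 per arm it is about 40–48% under the assumed sensitivities. For that reason, putting Hypothesis 2 behind a significant baseline test is not a minor step: with power below 50%, it would block the second-round claim in more than half of trials even if co-testing works as assumed. Holm avoids that dependence. If the sponsor prefers a fixed order, it should choose the round knowing these figures.

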**Hypotheses**

- There is a significant difference in the number of CIN2+ cases detected between the cytology testing group and the cytology-HPV co-testing group at baseline.
- Significantly more CIN2+ cases will be detected at the second round of screening among participants with normal cytology result in the control arm than those with normal cytology and negative HPV results in the intervention arm.
- Cases infected by certain HPV genotypes are at higher risk of developing CIN2+ or HGSIL than those infected by other HPV genotypes.

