***Control arm***

The index test for participants in the control arm will be conventional cytology testing. HPV testing will also be administered. ,HPV results will not be revealed to the participant or healthcare professionals who are involved in the direct care of the participant except in the case of reflex HPV testing for borderline cytology results. Participants will be managed based on their cytology results according to the current practice of the involved clinics and the Hong Kong College of Obstetricians and Gynaecologists Guidelines. (Fig. 1) Colposcopy will be offered in the following conditions: (1) any cytologic abnormalities greater than ASCUS, (2) ASCUS and HPV positive, or (3) two consecutive ASCUS results. In addition, a random 5% of participants with negative cytology results will be invited to attend colposcopy at baseline at the Lady Helen Woo Women’s Diagnostic and Treatment Centre.  Post colposcopy management of participants is shown in Fig. 2. Participation in the study will be terminated at a diagnosis of CIN 2 or greater.

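### Hypothesis 2 compares differently selected groups, so a second-round difference in the hypothesised direction is built in, and the comparison is not intention-to-treat

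*Protocol*

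**What the plan says.** Protocol, Hypotheses, second item: "Significantly more CIN2+ cases will be detected at the second round of screening among participants with normal cytology result in the control arm". The comparator is intervention women who are negative on both tests.

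Protocol, Data analysis, uses the same two groups for the second-round relative risk: control women with normal cytology, and on the other side a risk "for those in the intervention arm who have normal cytology and negative HPV results at baseline". The paragraph opens with "Data analysis will be performed according to the intention-to-treat principle" and names no exception. It also says "Incidence of CIN2+ will be calculated for both arms at baseline and at the second screening round" and "For proportion comparisons, chi-square tests will be employed", but attaches no second-round hypothesis to the whole-arm figures.

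Protocol, Control arm, says of the controls: "HPV testing will also be administered". Those results are concealed except where reflex testing follows borderline cytology. The HPV status of cytology-negative controls will therefore be known to the analyst.

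**The concern.** A control woman with normal cytology stays in the comparison whatever her HPV result. An intervention woman with normal cytology leaves it if she is HPV-positive. The two groups therefore differ in composition by construction, and randomisation does not balance them.

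The protocol's Introduction treats HPV as the cause of the disease, so the women removed from one side are the ones expected to be at higher risk. They are also the women on whom the two strategies differ most at baseline. Fig. 3 sends them to colposcopy in the intervention arm. In the control arm they are followed as cytology-negative, apart from the random 5% of that group invited to colposcopy. A comparison that drops them from one side cannot separate two explanations: that HPV testing sorts women by risk, and that acting on the result reduces later disease. What is at stake is the second-round conclusion about the strategy.

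**Working it through.** **No planned figure to reproduce.** The protocol gives no expected difference or power for Hypothesis 2. The 12,000 in Sample Size Calculation rests on baseline sensitivity.

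**Inputs from the protocol**
- Cytology-negative controls: 5544 (Fig. 1). Check: 5% × 5544 = 277.2, matching the 277 in Fig. 1.
- HPV-positive, cytology-negative intervention women: 240 (Fig. 3).
- CIN2+ prevalence 1.2%, sensitivity gain 25 points, loss 10% (Sample Size Calculation); 6000 per arm (Figs 1 and 3).

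**Assumptions not in the protocol**
- The cytology split is the same in both arms. The figures are consistent with this: abnormal cytology is 261 + 145 = 406 in Fig. 1 and 130 + 275 = 405 in Fig. 3, where the HPV-negative, above-ASCUS cell has no count.
- k, the second-round CIN2+ risk ratio of HPV-positive to HPV-negative women among the cytology-negative.
- The second-round risk in HPV-negative women, taken as 0.05% to 0.3%.
- The 10% loss applies equally to both groups.

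**Step 1: built-in relative risk (RR) with no strategy effect**

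f = 240/5544 = 0.0433, which leaves 5544 − 240 = 5304 double-negative women.

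RR = [f·k·r + (1 − f)·r]/r = 1 + f(k − 1), where r is the HPV-negative risk.

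| k | RR | Chance of a significant result in the hypothesised direction |
|---|---|---|
| 1 | 1.00 | 2.5% |
| 5 | 1.17 | 4–7% |
| 10 | 1.39 | 6–16% |
| 20 | 1.82 | 11–46% |
| 50 | 3.12 | 37–98% |

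The last column is for a two-sided 5% test of two proportions (normal approximation), with 0.9 × 5544 = 4990 and 0.9 × 5304 = 4774 women. With few cases the approximation is rough. A valid test would give 2.5% in that direction.

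If raw case numbers are compared, as the wording of Hypothesis 2 allows, the larger control group adds a further factor of 5544/5304 = 1.045.

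**Step 2: upper illustration from the planning figures**

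CIN2+ per arm = 0.012 × 6000 = 72. The extra cases that co-testing would detect are 0.25 × 72 = 18, all placed among the 240 women: 18/240 = 7.5%. The base sensitivity is not stated, so a range is shown.

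RR = [72(1 − s₁)/5544] / [72(1 − s₂)/5304]

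| s₁ v s₂ (assumed) | Control | Double-negative | RR | Implied k |
|---|---|---|---|---|
| 50% v 75% | 36/5544 = 0.65% | 18/5304 = 0.34% | 1.9 | 22 |
| 65% v 90% | 25.2/5544 = 0.45% | 7.2/5304 = 0.14% | 3.3 | 55 |
| 70% v 95% | 21.6/5544 = 0.39% | 3.6/5304 = 0.07% | 5.7 | 110 |

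This treats all CIN2+ missed at baseline as second-round yield, with no regression, no new disease and full detection. It also places every miss among cytology-negative women. Adding an assumed 0.3% of new cases to both groups in the middle row gives (0.45 + 0.30)/(0.14 + 0.30), or about 1.7.

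**Step 3: same rule on both sides**

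With no strategy effect and equal ascertainment, the expected RR is 1.00 for all randomised women by arm and for cytology-negative women in both arms with HPV-positive women kept in. It is also 1.00 for double-negative against double-negative, but those women are managed almost alike, so that contrast says little about the strategy.

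**The case against.** **The contrast answers a legitimate question.** Both groups are the women returned to a Pap test at three years (first column of Figs 1 and 3). Risk after a negative screen under each strategy bears on the screening interval, which the Introduction raises. This stands, and it is the reason to keep the contrast as a description. It does not make the contrast a randomised test.

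**Whole-arm second-round incidence is already planned.** It is, in the same paragraph as the intention-to-treat statement, and this limits the conflict to one comparison. An SAP that is not shown could settle details of testing. However, the protocol itself fixes the asymmetric groups twice, in the hypothesis and in the relative-risk sentence.

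**A significant result is not assured.** This stands. A reader might infer that Hypothesis 2 would be confirmed whatever the strategy does. The documents do not support that: the hypothesis asks for significantly more cases, and for k of 5 or 10 the chance stays at 16% or less. Only the direction of the expected difference is built in, and only if k exceeds 1.

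**Arm-level follow-up is not uniform.** Figs 2 and 4 give different post-colposcopy schedules, with repeat HPV testing only in the intervention arm. An arm-level second-round contrast therefore carries a difference in ascertainment. This stands and is met in the fix.

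**Conclusion.** The point holds for one comparison. The sole second-round hypothesis is tied to groups selected after randomisation by arm-specific rules. Its expected difference leans the hypothesised way with no strategy effect, and it contradicts the unqualified intention-to-treat statement.

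The built-in relative risk is about 1.2 to 3.1 for k from 5 to 50. The 1.9 to 5.7 from the planning figures is an upper illustration, not a forecast of the second round. Both rest on the assumed equal cytology split. The first also depends on k, and the second on unstated base sensitivities and complete carry-over of missed disease.

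A reader might go further and infer that the whole analysis breaks intention-to-treat, or that the trial cannot meet its aim. Neither follows. Whole-arm incidence is planned at both rounds, Hypothesis 1 is a whole-arm baseline comparison, and the stated aim and sample size concern detection of CIN2+.

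**What to change.** 1. Reword Hypothesis 2 so that its test is second-round CIN2+ among all women randomised, by arm. Data analysis already calculates this incidence.
2. Report it alongside cumulative CIN2+ over both rounds, because follow-up intensity differs between the arms (Figs 1 to 4).
3. Keep the stated contrast, labelled as a non-randomised description of risk after a negative screen.
4. As a supporting analysis, compare cytology-negative women in both arms with HPV-positive women kept in on both sides, stratified by HPV status using the concealed control-arm results.
5. Label any analysis restricted to women without CIN2+ in round 1 as a post-randomisation subset too, since detection in round 1 differs by arm.

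The cost is rewording one hypothesis and part of the Data analysis paragraph; no new data are needed. The arm-level contrast will probably be less extreme than the subset contrast.

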**Sample Size Calculation**

Based on the 2004-07 registry data from the Department of Health’s Cervical Screening Programme, the local prevalence of CIN2+ was postulated to be about 1.2%. A total sample size of 12000 women will be required to detect an absolute difference of 25% in the sensitivity between the control arm and the intervention arm in the detection of CIN2+ at 80% power and alpha = 0.05 (2-sided) and to account for an estimated 10% lost to follow-up rate.

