On the other hand, one study demonstrated that the use of HPV and cytology testings in primary screening increased the sensitivity of detecting CIN 3 or cancer by 35% (95% confidence interval [CI] 15 – 60%) with an insignificant decrease of PPV (relative PPV 0.76, 95% CI 0.52 – 1.10).[27] Meanwhile, other similar studies detected a substantial reduction in the PPV (relative PPV 0.55, 95% CI 0.37 – 0.82 for women aged 25 – 34; relative PPV 0.40, 95% CI 0.23 – 0.66 for women aged 35 - 60).[29, 30] A recent cohort study in Taiwan showed that the addition of HPV testing to cytology testing improved the sensitivity by 15.3% with a decrease of specificity by 9.6%, while the addition of conventional smear to primary high-risk HPV testing improved the sensitivity by 12.5% with a decrease of specificity by 0.5%.[31] The controversy of these studies makes it difficult to determine whether co-testing is cost-effective, and the complexity of different screening and follow-up strategies also fail to identify the best approach. In addition, there is no data on the performance of cytology and HPV testing in the local Chinese population. Therefore, our objective is to conduct a prospective study to compare the use of concomitant HPV-cytology testing with conventional cytology testing in primary cervical screening for the detection of high grade CIN among Hong Kong Chinese women.

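### The 80% power attached to 12000 women is for a difference in sensitivity; power for the first-listed hypothesis, CIN2+ detected per randomised woman, is not stated and is below 80% under most plausible inputs

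*Protocol*

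**What the plan says.** The Sample Size Calculation section of the protocol gives these inputs: "the local prevalence of CIN2+ was postulated to be about 1.2" per cent, taken from 2004-07 screening-programme registry data; a 25-point absolute difference in sensitivity; 80% power; two-sided alpha of 0.05; and "an estimated 10% lost to follow-up rate". It concludes: "A total sample size of 12000 women will be required to detect an absolute difference of 25% in the sensitivity". It names neither the sensitivity assumed in each arm nor the formula.

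Other sections set up a different comparison:

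- Outcome Measures: "Histological CIN2, CIN3 and cervical cancer are the primary outcomes of the study". Sensitivity appears there only as part of the fourth secondary outcome.
- Hypotheses, first item: "There is a significant difference in the number of CIN2+ cases detected" between the two groups at baseline.
- Data analysis: intention to treat; "For proportion comparisons, chi-square tests will be employed"; CIN2+ incidence is computed in each arm at baseline. Sensitivity is to be computed only from biopsies of women who have colposcopy at baseline.

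Figures 1 and 3 show 6000 women per arm.

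**The concern.** Sensitivity and detection rate have different denominators. Sensitivity is a proportion of women who have CIN2+, about 1.2% of each arm. The detection rate is a proportion of all women randomised to the arm. The same 25-point gain is a large difference on the first scale and a very small one on the second, so power computed on one does not carry over to the other.

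The denominator for sensitivity is also largely unobserved. Women negative on both tests in the intervention arm have no baseline biopsy. In the control arm only a random 5% of cytology-negative women (277 of 5544 in Figure 1) are invited to colposcopy.

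At stake is how a null result is read. If the first hypothesis is tested and not significant, a reader told that the trial had 80% power may conclude that co-testing detects no more disease, when the test had a much lower chance of showing a gain of the planned size.

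**Working it through.** **Inputs.** From Sample Size Calculation: prevalence 1.2%, difference 25 points, power 80% (z = 0.8416), two-sided 0.05 (z = 1.96), loss 10%. From Study Design and the figures: 1:1 allocation, 6000 per arm, so 6000 × 0.9 = 5400 after loss. Both are shown, because the first hypothesis is at baseline and by intention to treat. Control sensitivity is not stated. I assume 50–70% and also show 30–40%; the Introduction quotes 30–90% for cytology.

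**1. Reproducing 12000, with CIN2+ cases as the denominator.**

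n = [1.96·√(2p̄(1−p̄)) + 0.8416·√(p1(1−p1) + p2(1−p2))]² / (p2−p1)²

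For 50% v 75%, p̄ = 0.625: n = (1.342 + 0.557)² / 0.0625 = 57.7 cases per arm. With continuity correction, (n/4)·[1 + √(1 + 4/(n·0.25))]² = 65.4 cases per arm. Then 65.4 / 0.012 = 5452 women per arm, × 2 = 10905, / 0.9 = 12116. This is close to 12000, and 5400 × 1.2% = 64.8 cases agrees with it.

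The pair suggested by the Introduction (HPV testing above 90%, 25 to 30 points over cytology, so about 65% v 90%) gives only about 7900 without correction and 9300 with it.

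**2. Is that denominator observed?** Take 65% sensitivity and 6000 control women: 72 cases, of which 72 × 0.35 = 25 are missed. A 5% sample of cytology-negative women would find about 25 × 0.05, or roughly one. In the intervention arm, double-negative women are not sampled at all.

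**3. Power with women as the denominator.** Detection rates are 1.2% × sensitivity, so the difference is 1.2% × 25% = 0.30 percentage points whatever the control sensitivity.

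Power = Φ{[(p2−p1)·√n − 1.96·√(2p̄(1−p̄))] / √(p1(1−p1) + p2(1−p2))}

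For 65% v 90%, p1 = 0.0078 and p2 = 0.0108 (about 42 v 58 cases at 5400 per arm): (0.2205 − 1.96 × 0.1357) / 0.1357 = −0.336, so power is 37%.

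| Sensitivity, control v co-testing | Detected per woman | Power, 5400 / 6000 per arm | Power if 1.2% is the cytology-detected rate |
|---|---|---|---|
| 30 v 55% | 0.36 v 0.66% | 59 / 64% | 98 / 99% |
| 40 v 65% | 0.48 v 0.78% | 50 / 55% | 88 / 91% |
| 45 v 70% | 0.54 v 0.84% | 47 / 51% | 80 / 84% |
| 50 v 75% | 0.60 v 0.90% | 44 / 48% | 73 / 77% |
| 65 v 90% | 0.78 v 1.08% | 37 / 40% | 52 / 57% |
| 70 v 95% | 0.84 v 1.14% | 35 / 38% | 47 / 51% |

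In the last column the control rate is 1.2% and the co-testing rate is 1.2% × (s + 0.25)/s, for example 1.66% at s = 65%. Simulating the chi-square test on the stated-prevalence reading gives 44% at 50 v 75 and 35% at 70 v 95 with 5400 per arm. A continuity-corrected test lowers these to 40% and 32%.

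**4. Detectable rate ratio at 80% power.** On the stated prevalence it is 1.82 / 1.77 (5400 / 6000 per arm) at 50% control sensitivity and 1.68 / 1.64 at 70%. If 1.2% is a detected rate it is 1.55 / 1.52. The ratios implied by a 25-point gain are 75/50 = 1.50, 90/65 = 1.38 and 95/70 = 1.36.

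**The case against.** The strongest reply is that the low figures rest on two inputs the protocol does not settle. Control sensitivity is not given. The 1.2% is called a prevalence but comes from a screening registry, where the recorded figure could be disease that cytology found. On that second reading power is 47–77% for control sensitivity of 50–70% and passes 80% at about 45% or lower (about 48% with 6000 per arm). This stands, and it rules out a single unconditional figure. A reader might infer that a true 25-point gain would more likely than not be missed. That follows at 50–70% control sensitivity on the stated prevalence, but not at 30–40%, nor for most of the detected-rate reading.

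Other readings go further than the document allows:

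- That 12000 is an arithmetic error. It is not: plausible inputs reproduce it approximately. The problem is a mismatch of endpoint.
- That the sponsor used 50% v 75% with continuity correction. That is inferred; the protocol names no pair and no method.
- That Hypothesis 1 is declared primary. The three hypotheses are unranked and the primary outcome has no time point. It is listed first, and it compares the arms on the primary outcome.
- That power is only about 20%, because the Introduction reports that "the addition of HPV testing to cytology testing improved the sensitivity by 15.3" per cent in one cohort. The text does not say whether that gain is absolute or relative, and 25 points is the plan's own target.

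It may also be said that a paired analysis belongs in a statistical analysis plan. That is fair, so it is optional below. The power claim itself is in the protocol.

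**Conclusion.** The concern holds in conditional form. The stated 80% belongs to a comparison of sensitivities with unstated values, and it is approximately reproduced with about 65 known CIN2+ cases per arm as the denominator, which this design does not observe. No power is given for CIN2+ detected per randomised woman.

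For a 25-point gain, power for that comparison is about 35–48% with 1.2% read as true prevalence, as written, and control sensitivity of 50–70%. It is about 50–64% at 30–40%. On this reading it stays below 80% for every control sensitivity from 30% to 75%. If 1.2% is a cytology-detected rate, power is about 47–77% at 50–70% and exceeds 80% only when cytology sensitivity is about 45% or lower. All figures assume a two-sided 0.05 chi-square test without continuity correction and 5400 to 6000 women per arm.

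**What to change.** Keep 12000 and correct the Sample Size Calculation section:

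1. State the sensitivity assumed in each arm, and whether 1.2% is true prevalence or a detected rate.
2. Replace the 80% claim with the power for CIN2+ detected per randomised woman on those inputs, and give the detectable rate ratio (about 1.5–1.8).
3. State that a non-significant result on the first hypothesis does not show equal detection.

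Optionally, add a descriptive paired estimate within the intervention arm: among its detected CIN2+ cases, the share that the control arm's baseline referral rule would also have referred. It should carry two caveats. It is nested, so co-testing cannot do worse and the estimate sizes the gain without testing its direction. And the control arm's reflex HPV test is run in a different laboratory (HPV testing section), so the rule may not be exactly reconstructed.

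The cost is protocol wording and, if wanted, one extra descriptive analysis, with no additional women or visits. The stated power becomes less favourable. Holding 80% for the first hypothesis on the stated prevalence would instead take about 12983 (50 v 75%) to 17096 (70 v 95%) evaluable women per arm, or about 28900 to 38000 in total after 10% loss, so correcting the statement is the practical course.
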